**A.8 QUALITY ASSURANCE**

A.8.1 What procedures are in place to ensure the quality of the data?

*Guidance notes:*

*For qualitative data (for example) what procedures will be used to check translations or compare data obtained from different sources?*

*For quantitative data (for example) how will transcription errors be minimised?*

*Give some detail on how methods are going to be piloted, if appropriate*

The primary objective of our study is to assess the number of women who present to ANCs at the different facilities with or without the intervention. There will be ample staff available at triage to capture all of the patients who present to each clinic thus ensuring that the maximal data will be captured at each sMHC.

The same two research associates will deliver the maternal survey to every patient enrolled into the study with the help of the same two translators. This will ensure consistency in the questions being asked and the answers that are translated. The vast majority of the answers will be very simple “yes or no” and thus will be subject to very little inter-interviewer discrepancy.

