**A.5 PARTICIPANTS**

Please provide the following information on the participants with/from whom you expect to be collecting data:

A.5.1 Age / Sex: (please enter the expected number in each of the boxes)

|  | Neonates  (<28 days) | Infants  (1-11 months) | Young children  (1-9 years) | Adolescents  (10-17 years) | Adults  (18 yrs & above) |
| --- | --- | --- | --- | --- | --- |
| **Males** | **0** | **0** | **0** | **0** | **0** |
| **Females** | **0** | **0** | **0** | **0** | **550** |

A.5.2 What specific measures are in place to take into account women of childbearing age?

*Guidance notes:*

*Pregnant women may have different responses to disease processes*

*The developing foetus may be particularly vulnerable in intervention trials*

The main goals and objectives of this study revolve around recruiting pregnant women. However, given that all of the interventions being offered are standard of care and not experimental or dangerous in any way there will be minimal risk to this category of patients.

A.5.3 Describe how and where the participants are to be recruited?

*Guidance notes:*

*This is distinct from the statistical sampling method described in A.4. You should outline the procedures for recruitment of each group of participants, include details on:*

- *the setting (e.g. Country, Town, District, on the ward, out-patient department ,in the home)*
- *inclusion and exclusion criteria for selection, if relevant (e.g. “Women of child-bearing age will be excluded”)*

As described above, participants will be recruited from communities in the Kabale Region by announcements that will be made by community leaders at local schools, churches, and community events regarding the upcoming free antenatal clinics.

Inclusion criteria include:

The participants to must all be residents of the Kabale Region. All pregnant women who present to one of the sMHCs will be included.

Exclusion criteria include:

Any males or non-pregnant females who attend the health camps will be excluded from the study.*

Notes:

*All participants excluded from the study will still offered free medical and dental care as part of a mobile free medical/dental clinic that will be offered in the same community at the same time but in a neighbouring location.

A.5.4 Please justify your choice of sample size (as described in A.4)

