Sample size calculations were considered for two of the primary outcomes. For the first outcome – looking to determine the efficacy of portable ultrasound in improving maternal uptake of antenatal care due to portable ultrasound being offered – a simple randomization based on communities will be utilized. For the additional outcome of eliciting a change in patient preference for delivering at a healthcare facility before and after a rural outreach clinic the communities will be both clustered and randomized. In this case a design effect is added to account for the clustering for this patient-level outcome.

1. Facility based uptake of ANC (no clustering): At a two-sided alpha of 0.05 and holding power at 80%, with p1 of .70 and p2 of 0.52 [1], then 144 pregnant women will be required in each of the control and intervention groups. Inflating this by 25% to prepare for any non-consent and/or non-response, the required sample increases to 180 women per group. From experience gained in our pilot study, we anticipate that health facilities will enroll a greater number of women, therefore our sample will provide more than adequate power. We will conduct power calculations during analysis, however, we anticipate power of greater than 90%.
2. Patient-level outcomes (clustered): At a two-sided alpha of 0.05 and holding power at 80%, using an estimated intracluster coefficient (ICC) of 0.1 [2], with p1 of 0.95 and p2 of 0.85, and an average cluster size of 60 pregnant women (m), then 225 pregnant women will be required per study arm, which is equivalent to needing 4 clusters per group. Inflating this by 25% to account for potential non-response gives 282 pregnant women per group.

Notes:

1. Rate of uptake of antenatal care (at least 1 ANC visit) in pilot studies in our community
2. Generally, ICCs are not known prior to study start. For ICC assumption, it is generally accepted that clinical outcomes have ICCs of around .05; whereas process outcomes (which our research is studying) range from 0.05 to 0.15; we have used 0.1 in our calculations.

Reference: <http://www.who.int/reproductivehealth/topics/best_practices/intracluster_correlation.pdf>

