**5. Inclusion/Exclusion Criteria**

Inclusion:

The participants must all be residents of the Kabale Region. All pregnant women aged 18 and above who present to one of the sMHCs will be included.

Exclusion:

Pregnant women under the age of consent (under 18 years); and any males or non-pregnant females who attend the health camps will be excluded from the study.*

Notes:

*All participants excluded from the study will still be offered free medical and dental care as part of a mobile free medical/dental clinic that will be offered in the same community at the same time but in a neighbouring location. For pregnant women under the age of 18, fOBU will also be offered.

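### Uptake is sized as a proportion of community pregnant women, but only attenders are enrolled and the outcome is a count, so 144–180 enrolled women per group is not that denominator and the claim that more enrolment gives more power is invalid

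*Protocol*

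**What the plan says.** - **Sample size (A.5.4 item 1).** Uptake is a two-proportion comparison: "At a two-sided alpha of 0.05 and holding power at 80%, with p1 of .70 and p2 of 0.52 [1". The result is 144 women per group. The text continues "Inflating this by 25% to prepare for any non-consent and/or non-response" and reaches 180.
- **Meaning of the proportion (A.5.4 note 1).** "Rate of uptake of antenatal care (at least 1 ANC visit) in pilot studies in our community".
- **Power claim (A.5.4 item 1).** "we anticipate that health facilities will enroll a greater number of women, therefore our sample will provide more than adequate power". Power above 90% is anticipated.
- **Who is enrolled (A.5.3 and Section 5).** Only women who come. Section 5 reads "All pregnant women aged 18 and above who present to one of the sMHCs will be included".
- **Endpoint (A.8.1).** "The primary objective of our study is to assess the number of women who present to ANCs at the different facilities". The hypothesis (A.3 and Section 2) is also about a number of women.
- **Analysis (A.7.1).** Uptake is compared at health-centre level by linear regression with adjustment for potential confounders. No denominator is named.
- **Community data and allocation (A.4 and Section 3).** Communities are assessed for population size, demographics and birth rate. Similar ones are selected and then randomised within small, medium and large catchment strata. Section 3 registers all women who appear.

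**The concern.** The sample size and the endpoint describe different quantities. A rate of 0.70 or 0.52 needs pregnant women in the community as its denominator, including those who stay away. The trial enrols only those who come, so every enrolled woman has attended. Among 144 or 180 enrolled women per group, camp attendance is 100% in both arms.

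Two things are at stake. First, the assurance of more than 90% power for the main outcome is drawn from the outcome itself: high turnout in both arms is not extra information about the difference between them. Second, an outcome left as a raw count varies with the number of pregnant women in each catchment, as well as with the message they heard. With few communities per arm, that extra variation can be material.

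**Working it through.** **1. The plan's own figure.** Inputs from A.5.4 item 1: p1 = 0.70, p2 = 0.52, two-sided alpha 0.05, power 80%. With mean proportion 0.61:

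n = [1.960 × √(2 × 0.61 × 0.39) + 0.842 × √(0.70 × 0.30 + 0.52 × 0.48)]² / 0.18² = (1.352 + 0.571)² / 0.0324 ≈ 114.1, so 115 per group (125 with continuity correction).

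The stated 144 is not reproduced. It equals 115 × 1.25 = 143.75 after rounding, so the inflation may already be in it; that is a guess. The next step, 144 × 1.25 = 180, reproduces. Ignoring clustering, power is 88% at 144 and 94% at 180. These figures apply only if 144 or 180 counts all pregnant women sampled per arm, attenders or not.

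**2. What enrolment would look like under the plan's own rates.**
- If 180 is the community denominator, expected attenders are 180 × 0.70 = 126 and 180 × 0.52 = 93.6. Enrolment would differ by arm because it is the result.
- If 144 is the number enrolled in each arm, the catchments must hold 144 / 0.70 = 206 and 144 / 0.52 = 277 pregnant women. Equal enrolment from equal catchments would mean no effect at all.

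So the enrolled number cannot serve as the n in step 1, and a larger enrolment does not raise power as item 1 says.

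**3. How far raw counts depend on catchment size.** The planned ratio is 0.70 / 0.52 = 1.35. At equal uptake, 35% more pregnant women in the intervention catchments gives the same ratio. A shortfall of 26% (0.52 / 0.70 = 0.74) cancels a true effect of the planned size.

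**4. Illustration of the precision cost.** These assumptions are not in the protocol: 4 communities per arm (A.5.4 gives that number only for the other outcome), expected pregnant women 50/90/90/160 by stratum, beta-binomial attendance, and linear regression on arm and two stratum indicators (4 residual degrees of freedom). Each entry is power for 0.70 v 0.52 from 20,000 simulated trials, as raw count v proportion with an exactly known denominator.

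| Within-stratum variation in size (CV) | ICC 0.01 | ICC 0.05 | ICC 0.10 |
|---|---|---|---|
| 10% | 44% v 77% | 25% v 38% | 17% v 24% |
| 20% | 23% v 76% | 17% v 38% | 13% v 24% |
| 30% | 13% v 75% | 12% v 37% | 10% v 24% |

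At 30% variation the arm ratio of expected pregnant women has a 95% range of about 0.64 to 1.55.

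**5. If the denominator is itself uncertain.** At ICC 0.05 and 30% catchment variation, power for the proportion falls from 37% to about 20% with 20% error in each community's denominator, and to about 15% with 30% error. At 10% catchment variation and 20% error it is about 21%, below the 25% for raw counts.

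**The case against.** The other side is right on several points.

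- **A reader might infer that the trial cannot yield an uptake proportion at all.** The protocol does not support that. Population size and birth rate are assessed for every community, so an approximate denominator is within reach. What is missing is a statement that it will be used.
- **A reader might infer that arm differences are confounded with catchment size.** They are not, in the systematic sense. Similar communities are selected, allocation is randomised within size strata, and A.7.1 adjusts for confounders. Chance imbalance remains, and it costs precision. In the simulation with equal uptake of 0.60 and ICC 0.05, the stratum-adjusted test of raw counts rejected in about 4% of trials at 10% and at 30% catchment variation, so it does not produce excess false positives.
- **A reader might infer that consent or withdrawal after the debriefing changes the attendance count.** Section 3 registers all women who appear, and A.8.1 has triage capture everyone who presents. Nowhere is attendance limited to consenters; only the inflation line hints at it.
- **Under-18s.** A.5.3 has no age limit ("All pregnant women who present to one of the sMHCs will be included") and Section 5 has one, but A.5.1 expects no adolescents and Section 6 excludes them. This is a minor wording slip.
- **The power gains in the table are a best case.** They assume an error-free denominator and rest on catchment variation that selecting similar communities may reduce. Replacing the stratum indicators by exactly known catchment size, a covariate A.7.1 would permit, brings raw counts to about 32% at ICC 0.05 and 30% variation.

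The choice between an offset and a proportion, and the covariate list, may properly sit in an analysis plan that is not shown. None of this rescues the power sentence, which is wrong in the protocol itself, or the mismatch between the sized quantity and the enrolled sample.

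**Conclusion.** The point holds for the definition and the power statement. A.5.4 item 1 sizes a proportion among community pregnant women; the trial enrols attenders, and the primary objective is their number. Neither 144 nor 180 enrolled women per group is the denominator of 0.70 v 0.52, and the inference from greater enrolment to more than adequate power is invalid. This rests on the protocol's wording alone.

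Leaving the outcome as a raw count also costs precision through chance differences in catchment size. The direction follows from the design; the size does not. Against an exactly known denominator at ICC 0.05, the illustrated loss runs from 38% to 25% power at 10% catchment variation, and from 37% to 12% at 30%. With enough error in the denominator the advantage can disappear. These figures are illustrations under assumed inputs, not estimates for this trial.

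**What to change.** - Define the primary outcome per community as all pregnant women registered at triage, divided by the expected number of pregnant women in the catchment, derived from the population size and birth rate already assessed. State how a birth rate is converted to women pregnant at the clinic date. Equivalently, analyse counts with log expected pregnancies as an offset.
- State that triage registration counts every pregnant woman who attends. Restrict only the survey outcomes to consenting women aged 18 and above, and align the age wording of A.5.3 with Section 5.
- Delete the sentence linking greater enrolment to power, and the non-consent inflation for this outcome.
- Restate planning values and power for a community-level comparison, giving the number of communities, the ICC and the assumed catchment variation. The 144 should be re-derived or withdrawn at the same time.
- Add a sensitivity analysis to error in the denominator.

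The cost is protocol wording and a tally that Section 3 very nearly provides already. The downsides are that the denominator is an estimate and that the restated power will be less favourable than the figure now given.

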**A.9 DISSEMINATION OF RESULTS**

Please outline what plans you have for dissemination of results.

*Guidance notes:*

*Where possible a mechanism should be in place to inform study participants of the outcomes of the study.*

*It is important that study findings are made known to local services / policy makers before they are discussed (e.g.) at international scientific meetings*

Data regarding the number of women screened and the efficacy of ultrasound in attracting participants will be provided in informational sessions to community leaders and then to church and school groups. If the ultrasound is found to either A) identify important obstetrical complications that require intervention in one or more patients or B) enhance maternal presentation for care then the investigators undertake to carry out a fundraising campaign in Canada to purchase portable ultrasound devices and train local staff in the use of ultrasound at the end of the project. This will enable the community to have ongoing benefit from this intervention.

**SECTION B**

**CONSEQUENCES FOR THE LOCAL COMMUNITY / ENVIRONMENT AND PARTICIPANTS**

B.1 Outline the potential adverse effects, discomfort or risks that may result from the study in the following areas:

B.1.1 Participants

*Guidance note:*

*In addition to the physical effects of tissue sampling (for example blood sampling) it should be borne in mind that interviews and focus group discussions may sometimes trigger painful or distressing memories (e.g. questions about sexual practice or the death of a child)*

There is a potential for psychological/emotional risks on the participants from feeling embarrassed and/or uncomfortable with the ultrasound procedure. As well, there is a potential risk for false positive detection of fetal abnormality/maternal complication of pregnancy. HIV testing will be conducted, there is a risk for psychological well-being from this testing.

B.1.2 Investigators

*Guidance notes:*

*Include here (for example)*

- *the biomedical risks to investigators (including local staff) involved in tissue sampling (e.g. Hepatitis B, HIV)*
- *the psychological consequences for social science investigators exposed to narratives of violence or severe grief*
- *the risks from the environment (e.g. in a war zone)*

Given the nature of this study it is not anticipated that there will be any risk to the investigators.

B.1.3 Members of the public

Given the nature of this study it is not anticipated that there will be any risk to members of the public.

**B.2 Outline what steps will be taken to minimize the adverse effects, discomfort or risks described above.**

B.2.1 For participants

*Guidance notes:*

*In biomedical research, appropriate use of anesthesia prior to procedures (for example) is important.*

*For social science research it may be necessary to ensure that counseling services are available for those who re-live traumatic experiences through (for example) an in depth interview.*

1. To eliminate any emotional risks of feeling uncomfortable or embarrassed while receiving an obstetric ultrasound all scans will be conducted in a private room with a trained technician. If the technician is male gender the patient will have the right to request a female chaperone. No additional personnel will be able to observe the ultrasound scan unless they have received specific verbal consent from the patient.

Voluntary counseling and testing for HIV and sexually transmitted diseases will be provided as part of routine medical care. The risks associated with this approach are well documented but not altered by study involvement and is strongly advocated by all consensus national and international guidelines. All care will be provided as per Ugandan national guidelines.

1. In this case the intervention – a free obstetric ultrasound – has low risk for potential adverse outcomes. False positive screening ultrasound identifying non-existent congenital anomalies may lead to maternal concern. Any women who have an examination that demonstrates concerning findings will be transferred free of charge to a tertiary care facility for obstetrical consultation and confirmatory testing. Thus, the benefit of early identification and management of true positive tests with prevention of maternal and fetal adverse outcomes will outweigh the potential risk of rare false positive testing.

B.2.2 For investigators

*Guidance notes:*

*Where the research may involve adverse experiences for investigators (see B.3.2), de-briefing / support meetings may be important.*

N/a

B.2.3 For members of the public

N/a

**B.3 CONSEQUENCES FOR LOCAL HEALTH SERVICES**

B.3.1 What demands will this research place on local health services?

*Guidance notes:*

*For example, how much of a nurse’s usual work time will be taken up in acting as an interpreter for an outside investigator?*

The entirety of this study will be conducted by Kigezi Healthcare Foundation in collaboration with a Canadian not-for profit medical and dental organization TO – the WORLD (TOW). All research taking place will be conducted by staff and resources provided by TOW.

B.3.2 Detail how the design of the research project takes into account the demands described in 3.1.

*Guidance notes:*

*Disruption to routine services should be kept to a minimum.*

N/A

**B.4 CONFIDENTIALITY AND PRIVACY**

B.4.1 What steps will be taken to ensure privacy and confidentiality for participants?

Patient care data will be collected in clinical charts during the sMHC. This data will be stored in the local health care facilities as per usual practice. Specifically, all hard copy data obtained on the ground in Kabale will be stored in a locked cabinet in locked room at the KIHEFO offices, only KIHEFO medical staff have access to patient information.

Study data will be anonymized and replaced by a study number then kept on a password protected electronic database. This database will only be made available to the immediate study staff

The data will be kept for 7 years. Following this time period the protected electronic database will be deleted.

B**.5 INFORMED CONSENT**

B.5.1 Information given to participants:

Please indicate what you will tell the participants in simple language. The purpose of the study, type of questions that will be asked, and procedure or treatment which will be applied should be described and reference should be made to possible side effects, discomfort, complications and/or benefits. Please attach consent form typed on MUST-IRC official consent form.

| **It must be made clear to the participant that he/she is free to decline to participate or to withdraw at any time without suffering any disadvantage or prejudice.** |
| --- |

In the attached consent form you will find that we have explained to the patients that they are agreeing to participate in a research study regarding antenatal care in rural Uganda. We explain that they will still be able to receive all medical and dental services free of charge even if they decide to not participate in the research study. Following the completion of the consent form the patients will be asked a number of questions in our maternal survey form. Following completion of the maternal survey form the patients will be provided with a “debriefing” and final consent form. This form will explain to the patients that they were not initially informed as to the presence of ultrasound in the clinic so as to determine accurately their reason for coming to clinic that day. This form will also very clearly state that the patient has the right to refuse the ultrasound, withdraw from the study at any point, and still receive all medical and dental care free of charge at clinic that day.

B.5.2 Outline who will deliver the above information and how?

The information attached in the consent form will be delivered by highly trained and nationally certified KIHEFO nursing staff verbally and with the aid of a printed consent form.

B.5.3 Please indicate how consent will be obtained, given local circumstances.

*Guidance notes:*

*In some societies, the concept of giving consent on an individual basis is unfamiliar. It may be necessary to obtain consent both at community and individual level.*

*Obtaining consent from minors requires both consent from the guardian and, where possible, the minor.*

N/A

B.5.4 Are any inducements to be offered to either participants or the individuals who will be recruiting them? (e.g. improved patient care / cash) (please tick appropriate box)

Yes No

2

X

3

B.5.5 If yes, please give details:

N/A

B.5.6 Outline any hidden constraints to consent.

*Guidance notes:*

*Examples where hidden constraints may be important include:*

- *situations where participants are employees of the investigator*
- *patients who may feel their care could be compromised if they do not consent to research initiated by their carers.*

N/A

